## Abstract

**Background:**

Stroke is the most common disabling neurological condition in adults. Falls and poor mobility are major contributors to stroke-related disability. Falls are more frequent and more likely to result in injury among stroke survivors than among the general older population. Currently there is good evidence that exercise can enhance mobility after stroke, yet ongoing exercise programs for general community-based stroke survivors are not routinely available. This randomised controlled trial will investigate whether exercise can reduce fall rates and increase mobility and physical activity levels in stroke survivors.

**Methods and design:**

Three hundred and fifty community dwelling stroke survivors will be recruited. Participants will have no medical contradictions to exercise and be cognitively and physically able to complete the assessments and exercise program. After the completion of the pre-test assessment, participants will be randomly allocated to one of two intervention groups. Both intervention groups will participate in weekly group-based exercises and a home program for twelve months. In the lower limb intervention group, individualised programs of weight-bearing balance and strengthening exercises will be prescribed. The upper limb/cognition group will receive exercises aimed at management and improvement of function of the affected upper limb and cognition carried out in the seated position. The primary outcome measures will be falls (measured with 12 month calendars) and mobility. Secondary outcome measures will be risk of falling, physical activity levels, community participation, quality of life, health service utilisation, upper limb function and cognition.

**Discussion:**

This study aims to establish and evaluate community-based sustainable exercise programs for stroke survivors. We will determine the effects of the exercise programs in preventing falls and enhancing mobility among people following stroke. This program, if found to be effective, has the potential to be implemented within existing community services.

**Trial registration:**

The protocol for this study is registered with the Australian New Zealand Clinical Trials Registry (ACTRN12606000479505).

## Background

Stroke is a leading cause of death and disability. The annual estimated direct and indirect costs of stroke in the US in 2009 is $68.9 billion [1]. The major burden of stroke is chronic disability rather than death [2]. It is projected that stroke-related disability will increase dramatically over the next two decades as the population ages [3]. Development and implementation of effective strategies to minimise stroke-related disability is essential to minimise future health costs.

On completion of rehabilitation most stroke survivors can walk independently, however 90% of these people are unable to walk with sufficient speed or endurance to function effectively in the community [4] and 70% of stroke survivors will fall within six months of discharge from hospital [5]. Gait and balance problems have been found to be important risk factors for falls in stroke survivors [6,7]. Walking speed and walking capacity among community dwelling stroke survivors is markedly lower than age-matched controls [8,9], which results in major limitations of community participation.

Stroke typically affects older persons. The development of effective strategies to minimise disability and falls among older people is an urgent public health challenge due to the increase of older people in the global population. Around 500 million people worldwide are aged 65 and older and this number is predicted to increase to 1 billion by 2020 [10]. Falls adversely affect the quality of life of older people and can have serious consequences including fractures. Stroke survivors are four times more likely to suffer a hip fracture than other community-dwellers [11].

Systematic reviews in the general older population have found that exercise programs which specifically target balance and lower limb muscle strength are effective in preventing falls [12,13]. It is less clear whether exercise can prevent falls among people following stroke. There is also good evidence that well-designed exercise programs can enhance functional abilities after stroke [14]. Previous work has shown the effectiveness of small-group "circuit-style" exercise programs among people following stroke [15] or other disabling conditions [16] for improving mobility. Previously it was thought that recovery following stroke occurs within the first three months and is complete by 12 months [17]. However there is growing evidence that functional abilities can improve with exercise many years after stroke [9,18,19]

The Weight-bearing Exercise for Better Balance (WEBB) exercise program has been developed by two of the authors (CS and [name]) and colleagues to specifically target poor balance and lower limb muscles weakness for people at risk of falls. The main aim of this randomised controlled trial is to determine the effectiveness of the WEBB exercise program on reducing falls and enhancing mobility among community dwelling stroke survivors. In addition we will measure the effects of the program on risk of falling, physical activity levels, community participation, quality of life and health service utilisation. The WEBB program is available on request from the first author. A secondary aim of the trial is to evaluate the effect of the upper limb/cognitive intervention program, on upper limb function and cognition.

## Methods/design

### Design

A randomised controlled trial will be conducted with three hundred and fifty community-dwelling stroke survivors (Figure 1).

**Figure 1 F1:**
[figure not shown]
**Trial design**.

### Participant selection

Participants will be randomly assigned to one of two intervention groups and will be primarily recruited through the Stroke Recovery Association of New South Wales (NSW), Australia support group (Stroke Club) network. This Association holds regular Stroke Club meetings throughout NSW. The exercise classes will be conducted weekly in the venues used by the Stroke Club, prior to and after meeting times. It is anticipated that each Stroke Club will have participants randomised into both intervention groups and both types of classes will be offered at different times at the same venue. Additional participants will be recruited through advertisement and local physiotherapists and will attend the same exercise classes. To be eligible for the study, participants must be community-dwelling stroke survivors aged 40 years and above and be able to walk 10 m independently with or without a mobility aid.

Participants will be excluded if they have a Mini-Mental State Examination score [20] of < 20, have insufficient communication skills to participate in assessment and intervention, have a medical condition which precludes exercise (eg. unstable cardiovascular disease) or suffer from other uncontrolled chronic conditions that would interfere with the safety and conduct of the training and testing protocol.

All potential volunteers will be screened for eligibility by a physiotherapist. Medical clearance will be required from each participant's medical practitioner to certify him/her able to participate in moderate-intensity semi-supervised exercise before being accepted into the trial.

The study protocol has been approved by Sydney South West Area Health Service Ethics Committee (Clearance No: X06-0039) and The University of Sydney Human Research Ethics Committee (HREC Number 07/2006/9031), and written informed consent will be obtained from all participants.

### Measurements and Procedures

All participants will undergo two measurements: one on entry to the study (pre-test) and one after the 12-month period (post-test) by a physiotherapist blinded to group allocation. All pre-test measures will be completed prior to randomisation.

### Randomisation

After approval from the participant's usual General Practitioner and completion of the initial assessment, participants will be formally entered into the study and randomised to either the lower limb intervention or upper limb/cognition intervention group. Randomisation will be stratified by stroke club site using a computer generated random number schedule with variable block sizes 2–6. Generation of the randomisation sequence will be performed centrally by a researcher not involved in recruitment or assessment. Group allocation will be concealed using consecutively-numbered opaque envelopes. The opaque envelope will be opened after completion of the assessment in the presence of the participant.

## Intervention groups

Both intervention groups will receive weekly exercise classes and a home program for twelve months. The home programs will be reviewed monthly by a physiotherapist and modified if necessary.

### Lower limb group

The lower limb intervention group will receive an exercise intervention designed to prevent falls, enhance mobility and increase physical activity. This will involve a weekly circuit-style group exercise class, a home exercise program and a walking program. Interventions will be tailored to an individual's functional ability and the nature and difficulty of exercises will be progressed regularly.

The lower limb group will undertake exercises from the WEBB program. Participants will participate in a weekly exercise classes conducted by a physiotherapist and will be asked to perform a home exercise program at least 3 times a week. The home program and exercise classes include a 45–60 min program of progressive balance, lower limb strengthening exercises and walking. The exercise classes and home program will include 5 minutes warm-up exercises. The lower limb extensor muscle groups, which act to prevent collapse of the lower limb (hip and knee extensors and ankle plantarflexors) will be targeted with exercises designed to enhance balance and muscle strength. The balance exercises include standing with a decreased base of support, forwards and sideways stepping/walking, and graded reaching activities in standing. Strengthening exercises will include sit-to-stand, forward or lateral step-ups onto a small block, semi squats and heel raises in standing. Resistance for strengthening exercises will be applied using weighted vests in a similar protocol to one which has been successfully used by people with multiple sclerosis in a home-based program [21]. Standard principles governing frequency, volume, duration, intensity and progression of exercise will be applied [22].

### Upper limb/cognition group

The upper limb/cognition intervention group will receive a weekly exercise class aimed at management and improved function of the affected upper limb and cognition, carried out in the seated position. They will also be given a home exercise program. The upper limb component of the intervention was designed and developed by one of authors RB. We postulate that this intervention may lead to improvements in upper limb function and cognition but is unlikely to affect change in falls and mobility. This study design will, therefore, enable assessment of additional benefits of the lower limb intervention over and above likely benefits of social aspects of exercise classes.

### Safety

Participants will be instructed how to perform exercises safely with a stable object (such as a table) located nearby for additional support if required. Participants will be provided with a booklet containing safety precautions, instructions and photographs of exercises for use in exercise sessions at home. In addition, they will be provided with a logbook for recording exercises completed, effects of exercise (e.g. muscle soreness). Where appropriate, family members and/or carers, will be encouraged to assist with supervision and performance of the exercise program.

### Outcome measures

The primary outcome measures will be falls and mobility. Falls will be defined as "events that resulted in a person coming to rest unintentionally on the ground or other lower level, not as the result of a major intrinsic event or an overwhelming hazard" [23]. Falls will be assessed by comparing the number of falls in intervention and control groups. The proportion of fallers in each group will also be compared. Falls will be monitored for one year with monthly fall calendars. All participants will receive monthly calendars on entry to the study, with instructions to record the following events: number of falls, visits to or by nursing and allied health personnel, general practitioner or specialists appointments and hospitalisations. Participants will be asked to return the completed calendar monthly at their weekly exercise class. If calendars are not returned, further contact will be made by telephone. Details of any falls (including how and where the fall occurred, injuries suffered, medical intervention required and limitations to activity as a result of a fall) will be verified.

Two aspects of mobility, walking speed and capacity will be assessed. Walking speed will be measured using the 10 m walk test. Participants will be timed as they walk at their comfortable speed over the middle 10 m of a level 14 m walk track. Walking capacity will be measured by the distance covered in the 6 min walk test. The test will be conducted over a 25 – 30 m level corridor and standardised instructions will be given to each participant prior to the test and standardised encouragement at each minute in accordance with the American Thoracic Society guidelines for the 6 min walk test [24]. For safety, while administering this test, the assessor will walk slightly behind, and not beside, the participant so as to avoid influencing the participant's self selected walking pace.

Secondary outcome measures listed below will be collected on entry and at the end of the 12-month study period. These outcome measures will be

i) Falls risk assessed using the Physiological Profile Assessment [25]

ii) Physical activity assessed via a 7-day pedometer count

iii) Community participation using the Adelaide activity profile [26]

iv) Quality of life and well-being using the SF 12™ Version 2

v) Health service utilisation using monthly calendars

vi) Upper limb function using Items 6,7,8 of Motor Assessment Scale for Stroke [27] and the nine hole peg test [28]

vii) Cognition using the Montreal Cognitive Assessment [29].

### Statistical analysis

The number of falls per person-year will be analysed using negative binomial regression to estimate the difference in fall rates between the two groups, adjusted for previous multiple faller status [30]. The proportion of fallers between groups will be compared using the relative risk statistic. Between-group comparisons of final test performance for the continuously-scored outcome measures will be made using General Linear Models (ANCOVA) controlled for pre-test performance. Ordinally-scored data will be analysed for between group differences using the non-parametric Mann Whitney U statistic. An intention-to-treat approach will be used for all analyses.

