### Sample size

As fall rates will be compared between groups using incident rate ratios (IRR) from negative bionomial regression models [30] we conducted an analysis of statistical power using the nbpower command in the STATA software package. A total of 350 participants (175 per group) will be recruited. The study will have 80% power to detect as significant at the 5% level a 34% reduction in the rate of falling (i.e. an IRR of 0.66 using negative binomial regression analysis) in the 12 month follow-up period. This allows for a 15% loss to follow-up due to death or withdrawal from the study. Experience from our previous work indicates that, with this sample size, power will also be sufficient to detect meaningful between-group differences for all other outcome measures [9,15,16].

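### Neither the models nor the 80% power figure allows for correlation within the separate weekly classes of each arm; both are optimistic if class-specific correlation is more than trivial

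*Protocol article*

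**What the plan says.** Participants are randomised one by one, stratified by stroke club site (Randomisation). Each arm then has a weekly class and a home program for twelve months (Intervention groups). The classes are separate by arm within a club: "both types of classes will be offered at different times at the same venue" (Participant selection).

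For the analysis, "The number of falls per person-year will be analysed using negative binomial regression to estimate the difference in fall rates between the two groups" (Statistical analysis). The one covariate named is whether the person had previously fallen more than once. Continuous outcomes, which include the two walking tests that share primary status with falls, are compared by ANCOVA with the pre-test value as the only covariate. Neither model has a term for site or class.

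For power, "A total of 350 participants (175 per group) will be recruited", and "The study will have 80% power to detect as significant at the 5% level a 34% reduction in the rate of falling", that is, "an IRR of 0.66 using negative binomial regression analysis" (Sample size). The only allowance described is for attrition: "This allows for a 15% loss to follow-up due to death or withdrawal from the study". No class size, number of classes, ICC or design effect is given.

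**The concern.** Randomising individuals does not keep their outcomes independent once treatment is given in groups. People in one class share sessions, pace of progression and attendance habits for a year. Completed fall calendars are also handed in at the class, so recording of a primary outcome partly runs through it. A class belongs to one arm only, so whatever is peculiar to it adds noise to the treatment comparison that an individual-level model does not count.

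At stake are the confidence intervals and p-values for fall rate and for both walking outcomes, and the 80% power figure. The Discussion relies on that figure when it presents the trial as large enough to detect an effect on falls.

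**Working it through.** **Inputs from the article.** 175 per arm; 15% loss; IRR 0.66; 5% level (taken as two-sided, since this is not stated); 80% power; one year of follow-up. **Assumptions, because the article gives no figures:** equal class size m, class-specific (site-by-arm) ICC ρ_class, and ICC shared by both arms of a site ρ_site.

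**1. The stated 80%.** It cannot be reproduced, because the control fall rate μ0 and the dispersion k are not given. It can only be solved backwards.
- Implied standard error of the log rate ratio: |ln 0.66| / (1.960 + 0.842) = 0.4155 / 2.802 = 0.1483.
- Analysed per arm after loss: 175 × 0.85 = 148.75.
- Implied 1/μ0 + 1/μ1 + 2k = 148.75 × 0.1483² = 3.27.
- This corresponds to k of about 0.38, 0.80 or 1.01 at a control rate of 1.0, 1.5 or 2.0 falls per year.

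So 80% is attainable if participants are independent, but no margin for clustering is evident.

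**2. Design effect.** With total variance set to 1, the difference between the two class means at a site has variance 2 × [ρ_class + (1 − ρ_class − ρ_site)/m]. Under independence it is 2/m. The ratio is

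DE = 1 + (m − 1) × ρ_class − ρ_site.

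The shared site term lowers DE; the class term raises it and is multiplied by m − 1. With ρ_class = 0 and ρ_site of 0.02 to 0.05, DE is 0.98 to 0.95, so the planned standard errors would be slightly too large. With m = 8, a ρ_class of 0.01 contributes 0.07, which outweighs any ρ_site below 0.07.

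**3. Consequences with m = 8 and ρ_site = 0.**
- Power of a correctly clustered test: Φ(2.802/√DE − 1.960).
- Type I error of the planned test: 2 × [1 − Φ(1.960/√DE)].
- Chance that the planned test rejects at IRR 0.66: Φ(0.842/√DE).

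| ρ_class | DE | Power, clustered test | Type I error, planned test | Planned test rejects at IRR 0.66 |
|---|---|---|---|---|
| 0.01 | 1.07 | 77.3% | 5.8% | 79% |
| 0.02 | 1.14 | 74.7% | 6.6% | 78% |
| 0.05 | 1.35 | 67.4% | 9.2% | 77% |

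The third and fourth columns describe different tests and should not be read as one analysis. The planned test keeps most of its rejection rate by giving up control of type I error.

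**4. Range.** From m = 5 with ρ_class 0.01 (DE 1.04) to m = 12 with ρ_class 0.05 (DE 1.55), clustered power runs from 78.4% to 61.4% and unclustered type I error from 5.5% to 11.5%. With m = 8, clustered power drops below 78% once ρ_class exceeds about 0.007.

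**5. Simulation check of direction.** Unclustered negative binomial analysis, 3,000 runs, assuming 19 sites, 8 per class, 1.2 falls per year and k = 0.59. Type I error was:
- 5.2% with no clustering;
- 4.4% with shared site variation only (log-rate SD 0.4);
- 7.6% with class-by-arm SD 0.2.

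Taking the per-person log-rate variance as 3.27/2 = 1.636, an SD of 0.2 is an ICC of 0.04/1.676 = 0.024. The formula then gives DE 1.167 and a type I error of about 7%, in line with the simulation.

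**The case against.** **The size is unknown.** No ICC, class size or number of classes is given. A reader might infer that the standard errors are certainly too small and that the true power is well below 80%. The article does not support that: it depends on a class-specific ICC that nobody has stated, and at an ICC of 0.01 the distortion is small.

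**Stratification helps.** Randomisation within site removes whatever both arms of a club share. If one therapist ran both classes at a venue, a general therapist effect would largely drop out too. The article says a physiotherapist conducts the lower limb classes, but it names no leader for the upper limb classes. This stands, and it is why only the class-specific component counts.

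**The class effect may be diluted.** The lower limb arm exercises at home at least three times a week against one class, with tailored exercises. The seated comparator is not expected to alter falls or mobility, so its classes may vary little. If only lower limb classes vary, the excess in DE halves. At m = 8 and ICC 0.01 / 0.02 / 0.05, DE is 1.035 / 1.07 / 1.175, clustered power about 79% / 77% / 73%, and unclustered type I error about 5.4% / 5.8% / 7.1%. This also stands as a reason for moderation.

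**Larger figures can be produced.** A class-by-arm SD of 0.4 on the log rate gave a simulated type I error of 14.8%. That corresponds to an ICC of about 0.16/1.796 = 0.089, beyond the 0.01 to 0.05 range used here, so it should not be the headline.

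**A statistical analysis plan may deal with it.** The choice of variance estimator is often left to that document, and the article condenses a fuller protocol. This answers part of the point on the models. It does not answer the power statement, which is fixed in the article with attrition as its only allowance.

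**Conclusion.** The concern holds in conditional form. The article establishes separate weekly classes by arm and states models and a power figure without any class-level allowance. Standard errors are too small and power is overstated whenever (m − 1) × ρ_class exceeds ρ_site. The working figures are those for 8 per class: clustered power of about 77%, 75% or 67%, and unclustered type I error of about 5.8%, 6.6% or 9.2%, at a class ICC of 0.01, 0.02 or 0.05. They rest on an assumed class size and ICC, on ρ_site = 0, on equal class-level variation in both arms, and on taking the stated 80% as correct under independence.

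Confidence is high that no allowance is stated, and moderate about how much it matters. Severity is moderate: inference on both primary outcomes is affected, but neither the randomisation nor the sample size is put in question. Nor does the calculation count all 350 as analysed; with 15% loss the implied information is 350 × 0.85 = 297.5, about 298 participants.

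**What to change.** - **Models.** In the negative binomial model and the ANCOVA, include site, since it is the stratification factor, and a random intercept for class (site by arm). Alternatively, use class-clustered standard errors with a small-sample correction.
- **Data.** Make sure the class each participant is assigned to is recorded, with analysis by assigned class.
- **Sample size section.** State the assumed class size and class ICC and restate the power for IRR 0.66, for example about 75% with 8 per class and an ICC of 0.02. Leave the number recruited as it is.

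**Cost.** Changes of wording, somewhat wider confidence intervals and a slightly lower stated power. No extra participants or assessments are needed. If the class-specific correlation proves negligible, little precision is lost.

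### The fall-rate model adjusts only for a yes/no fall history and leaves out the fall-risk score measured at entry, so some precision on the powered outcome goes unused

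*Protocol article*

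**What the plan says.** Under Statistical analysis, the Protocol article fixes negative binomial regression as the method for the fall rate. The estimate is to be "adjusted for previous multiple faller status", and no other covariate is named for this model. In the same section, continuous outcomes are compared by ANCOVA with their own pre-test value as covariate.

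Under Outcome measures, the first secondary outcome is "Falls risk assessed using the Physiological Profile Assessment", and the list is introduced by "Secondary outcome measures listed below will be collected on entry and at the end of the 12-month study period". Measurements and Procedures adds: "All pre-test measures will be completed prior to randomisation". The score is therefore a legitimate baseline covariate.

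The Background gives a reason to expect it to carry information: "Gait and balance problems have been found to be important risk factors for falls in stroke survivors".

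Sample size sets recruitment at 350, split equally, and powers the trial on the fall rate: "The study will have 80% power to detect as significant at the 5% level a 34% reduction in the rate of falling". This is an incidence rate ratio (IRR) of 0.66, with 15% loss allowed for. The section gives no control fall rate, no dispersion and no gain from covariates.

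**The concern.** Previous falls are the nearest thing the trial has to a baseline value of its fall outcome. If multiple means two or more (the article does not define it), the yes/no variable treats someone with 2 previous falls like someone with 12, and someone with none like someone with 1. The continuous outcomes keep their full pre-test value, while the only outcome with a stated power calculation gets a two-level proxy. A pre-randomisation measure built to assess fall risk is also left out.

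In a negative binomial model, differences between people in fall propensity enter the variance of the log rate ratio through the dispersion. Baseline variables that explain part of those differences reduce the SE. With a log link, the rate ratio being estimated stays the same. What is at stake is precision, not validity.

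**Working it through.** **Inputs from the Protocol article (Sample size; Outcome measures).** 175 per group; 15% loss, so n = 175 × 0.85 = 148.75 per arm; IRR 0.66, with |ln 0.66| = 0.4155; power 80%; alpha 5%; one year of follow-up. Assumed: a two-sided test and a full year of exposure for those retained.

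**Step 1. The plan's own figure.** With control rate μ (falls per year) and dispersion k,

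Var(log IRR) = [1/μ + 1/(0.66μ) + 2k] / n = [2.515/μ + 2k] / 148.75.

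80% power requires Var = (0.4155 / (1.960 + 0.842))² = 0.0220, so 2.515/μ + 2k = 3.272. Neither μ nor k is given, so the 80% cannot be reproduced uniquely. These pairs all yield it:

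| μ | 1 | 1.5 | 2 | 3 |
|---|---|---|---|---|
| k | 0.38 | 0.80 | 1.01 | 1.22 |

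Below μ of about 2.515/3.272 = 0.77 it cannot be reached. The stated power is neither confirmed nor refuted.

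**Step 2. Formula check.** Start from 80% and let better covariates remove a further share of k:

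| Share of k removed | μ = 1, k = 0.38 | μ = 1.5, k = 0.80 | μ = 2, k = 1.01 |
|---|---|---|---|
| 10% | 80.9% | 81.9% | 82.4% |
| 20% | 81.8% | 83.9% | 84.9% |
| 30% | 82.7% | 85.8% | 87.3% |

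The lower the fall rate, the less there is to gain, because Poisson variation then makes up more of the variance.

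**Step 3. Simulation: yes/no status replaced by log(previous falls + 1).** 500 trials per setting, 149 per arm, IRR 0.66, dispersion 0.8 to 1.2. Here r is the assumed correlation between past and future fall propensity. Power = Φ(0.4155/SE − 1.96).

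| μ | r | SE, yes/no | SE, log count | SE reduction | Power, yes/no | Power, log count | Gain (points) |
|---|---|---|---|---|---|---|---|
| 1.5 | 0.6 | 0.1444 | 0.1427 | 1.2% | 82.1% | 82.9% | 0.9 |
| 1.5 | 0.9 | 0.1385 | 0.1332 | 3.8% | 85.1% | 87.7% | 2.6 |
| 2 | 0.6 | 0.1411 | 0.1382 | 2.1% | 83.8% | 85.2% | 1.5 |
| 2 | 0.9 | 0.1326 | 0.1238 | 6.6% | 88.0% | 91.9% | 3.9 |
| 3 | 0.6 | 0.1395 | 0.1349 | 3.3% | 84.6% | 86.9% | 2.3 |
| 3 | 0.9 | 0.1277 | 0.1124 | 12.0% | 90.2% | 95.9% | 5.7 |

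Worked example, first row: 0.4155/0.1444 = 2.878 and Φ(0.918) = 82.1%; 0.4155/0.1427 = 2.912 and Φ(0.952) = 82.9%.

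**Step 4. Independent simulation: yes/no status replaced by log count plus a hypothetical risk score.** Lognormal frailty, 149 per arm, 300 runs in each of nine scenarios, score-to-frailty correlation 0.2 to 0.4, history-to-frailty correlation 0.7 to 1.0. The SE fell by 0.5 to 2% at μ = 1, 2 to 7% at μ = 1.5 and 4 to 11% at μ = 2. Power gains ran from about 0 to 8 points, mostly under 3, with Monte Carlo error of about 2 points on each power. The estimated IRR stayed at about 0.66 under every model.

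Adding only the score to the yes/no model, at μ = 2 and a score correlation of 0.4, took the SE from 0.1330 to 0.1291 (2.9%) with history correlation 0.7, and from 0.1275 to 0.1247 (2.2%) with 1.0. That correlation is an assumption. The article does not say how well the Physiological Profile Assessment predicts falls, so these figures do not measure its contribution.

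**The case against.** The strongest reply is that nothing here is wrong. The plan prespecifies a valid model with a prognostic covariate, and there is no bias, contradiction or type I error problem. The 80% claims no help from covariates, so nothing promised is lost. All of that stands. A reader might infer that the primary analysis is defective or the trial underpowered because of this choice. The article does not support that: in every row of step 3 the yes/no model already has 82 to 90% power, and the largest gain comes where it is already at 90%.

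A second reply is that the gain is easily overstated. A reader might expect 2 to 7 points, but the SE pairs give 0.9 to 5.7, and only 0.9 to 2.3 at a correlation of 0.6. Larger gains need a correlation of 0.9, for which the article gives no support. A rate of 1 fall per year with k = 0.38 also reproduces the 80%, and there the benefit nearly vanishes. This reply stands in full.

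Third, a reader might assume that deriving multiple-faller status means a count is on file. It does not: 0, 1 or 2+ is enough, or even one yes/no question. The article mentions neither a count nor a recall window, so the log-count part is conditional. The baseline-score part is not, since that score is collected anyway.

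Finally, the article may condense a fuller covariate list. That is possible, but the sentence as published names one covariate, and the suggestion applies to that sentence.

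**Conclusion.** The point holds as an optional improvement in efficiency of low severity. The fall-rate model uses a dichotomised history and omits a fall-risk score measured before randomisation. Richer adjustment gave a smaller SE in every scenario run and left the IRR unbiased.

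The size is small to moderate and cannot be settled from the article. Moving from yes/no to log count lowers the SE by about 1 to 12% and adds about 1 to 6 power points at assumed rates of 1.5 to 3 falls per year, or about 1 to 2 points at a correlation of 0.6. At about 1 fall per year the SE reduction is 0.5 to 2%, even with a risk score included. These figures rest on the assumed rates, dispersions and correlations, a two-sided 5% test, and 149 per arm with a full year of exposure. The Physiological Profile Assessment's separate contribution remains unquantified.

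**What to change.** Before any outcome data are seen by group, amend the fall-rate sentence under Statistical analysis to:

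- add the baseline Physiological Profile Assessment score as a covariate in the negative binomial model;
- replace multiple-faller status by the finest fall history recorded: log(count + 1) if a count is held, otherwise the three levels 0, 1 and 2+;
- keep the model with multiple-faller status alone as a sensitivity analysis;
- state how a missing baseline score or history is handled, so that no randomised participant drops out of the analysis because of a covariate.

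The score needs only a change of wording, because it is already collected. The history part is also only wording if a count or three levels are on file. If only yes/no was asked, a finer history means one more question at entry for people not yet enrolled; failing that, the yes/no variable stays and only the score is added. Recall error in the count reduces the gain but does not bias the randomised comparison. The log form limits the pull of very large counts but does not remove it, so the fit should be checked.
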